### Statistical considerations

In all analyses, participants randomized will be analyzed according to the group to which they were allocated. All ratios and differences will be calculated as the experimental group compared to the control group. These analyses may be modified in the final statistical analysis plan at any time prior to the investigators accessing the study data in an unblinded fashion. The between-group differences in frequencies will be expressed as either absolute risk differences and their associated 95 % confidence intervals and/or by calculating the odds ratio and its associated 95 % confidence interval (exact binomial method). The between-group differences in continuous variables between groups will be assessed using repeated measures analyses. Sensitivity analyses will be performed by assessing the treatment effect after adjusting for baseline risk factors of known or highly suspected association with modality choice. These factors will include age, sex, diabetes mellitus status, socioeconomic strata, availability of a caregiver, presence of cognitive impairment (assessed by the Montreal Cognitive Assessment (MoCA) score [22], frailty [23], health literacy [24], and other comorbidities. To avoid model over-fitting, we will include only an appropriate number of variables (no more than one per 12 home-based dialysis events) and include them in the order in which they are written above. A two-sided *p* value of <0.05 will be regarded as significant without adjustment for multiple comparisons. The baseline probability of selecting home-based dialysis is assumed to be 28 % based on local data. Assuming an alpha value of 0.05, and 80 % power to detect a 22 % absolute difference between the intervention and usual care groups in the proportion of participants starting home-based dialysis, it is estimated that 152 participants would need to initiate dialysis to detect a significant difference between groups. Based on analysis of historical local clinic data on transition rates to ESRD therapies, it is anticipated that 264 participants will need to be recruited and followed for at least 1 year to achieve the required number of events. This recruitment target will be re-evaluated periodically and adjusted as needed based on differences between projected and when actual dialysis starts relative to the total number of recruited participants.

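### The plan does not say which effect measure decides; if the exact odds-ratio interval does, power at 152 dialysis starters is about 76%, not 80%

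*Protocol article*

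**What the plan says.** All of the relevant text is in the protocol article, under Statistical considerations.

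- **Design assumptions.** "The baseline probability of selecting home-based dialysis is assumed to be 28 % based on local data". The trial is sized with "80 % power to detect a 22 % absolute difference between the intervention and usual care groups" at alpha 0.05, and 152 dialysis starters are said to be needed. No sample-size formula is named.
- **Scale of the design effect.** It is an "absolute difference between the intervention and usual care groups in the proportion of participants starting home-based dialysis".
- **Measures.** The "between-group differences in frequencies will be expressed as either absolute risk differences" with 95% intervals and/or as an odds ratio with its 95% "confidence interval (exact binomial method"; the parenthesis closes the sentence.
- **Decision threshold.** "A two-sided *p* value of <0.05 will be regarded as significant". No test is attached to this threshold for the primary comparison.
- **Status.** The section reserves the right to modify these analyses in the final statistical analysis plan until the investigators have unblinded access to the data.

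**The concern.** The sample size is calculated on the risk-difference scale and matches a large-sample approximation. The only interval method named in the analysis text is exact and is attached to the odds ratio. In its usual conditional form that interval is conservative: its real error rate is below 5%, so it rejects less often than the approximation assumes.

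Two things follow if the text stands. First, the stated 80% depends on which of the two permitted measures turns out to decide, and the text does not fix that. Second, the measures are in effect two decision rules that can disagree at 0.05 on the same data. In a trial with one primary outcome, this leaves room to choose the favourable answer after the event.

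**Working it through.** **Inputs.** From Statistical considerations: control rate p1 = 0.28; difference 0.22, so p2 = 0.50; two-sided alpha 0.05; power 80%; 152 starters. Assumed: 1:1 allocation (the article does not give the ratio), so 76 starters per arm.

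**Step 1: reproduce 152.** Pooled normal approximation without continuity correction, with mean rate 0.39:

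n per arm = [1.960 × √(2 × 0.39 × 0.61) + 0.842 × √(0.28 × 0.72 + 0.50 × 0.50)]² / 0.22²
= [1.960 × 0.6898 + 0.842 × 0.6720]² / 0.0484 = 75.97, rounded up to 76 per arm, 152 in total.

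The formula's own power at 76 per arm is 80.0%. The arcsine method gives 75.6, also 76 per arm, so the formula actually used cannot be identified. The unpooled formula gives 74 per arm (148). The continuity-corrected formula, which approximates a conditional exact test, gives 84.8, or 85 per arm (170).

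**Step 2: power of each candidate rule at 76 per arm.** Sum Bin(a; 76, 0.28) × Bin(b; 76, 0.50) over all 77 × 77 outcomes (a, b) for which the rule declares p < 0.05.

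| Rule | Power at 28% vs 50% |
|---|---|
| Fisher's test, or conditional exact odds-ratio interval (doubled tail) | 76.2% |
| Mid-P | 79.7% |
| Unconditional exact (Barnard-type, score statistic) | 79.7% |
| Pearson chi-square (score test of no difference) | 81.0% |
| Wald risk difference | 81.5% |

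With both arms at 28%, the conditional exact rule has a true two-sided error of 3.3%.

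**Step 3: starters the conditional exact rule would need.** Power is 79.4% at 84 per arm and 80.2% at 85. So 170 starters are needed, 18 more than the stated 152.

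**Step 4: how often the two measures disagree.** The same enumeration, restricted to outcomes where the Wald 95% interval for the risk difference excludes 0 but the conditional exact odds-ratio interval includes 1, gives 5.2% of trials under 28% vs 50%. With both arms at 28% it gives 2.0%.

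**An example.** Take 21/76 (27.6%) against 33/76 (43.4%).
- Risk difference: 12/76 = 0.158. Standard error = √[(21 × 55 + 33 × 43)/76³] = 0.0766. The 95% interval is 0.158 ± 1.960 × 0.0766, or 0.008 to 0.308, which excludes 0.
- Conditional exact: twice the hypergeometric upper tail (33 or more of the 54 events falling in one arm of 76 out of 152) gives p = 0.062, so the odds-ratio interval includes 1.

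The same data are significant on one permitted measure and not on the other.

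**The case against.** The strongest reply is that the article never commits the primary test to an exact method. The words describe how an interval is calculated, in a sentence about how differences will be expressed. The risk difference is listed first and is the scale of the sample size, and on it the stated 80% is met among starters (81.0% to 81.5%). This stands. A reader might infer that the trial simply has 76% power instead of 80%, but the document does not support that: the 76% applies only if the conditional exact interval or Fisher's test decides.

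Nor does the word exact by itself imply 76%, since an unconditional exact test keeps 79.7%. This also stands. For an odds ratio, though, the conventional exact interval is the conditional one, so 76% is the natural figure for the method as worded.

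A third reply is that the choice of primary measure belongs in the statistical analysis plan, which is not shown, and that the article allows changes there. This stands in part. It means the matter can still be settled before unblinded access. It does not make the present text coherent, because the article itself sets out two measures and one interval method beside a single power figure.

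A fourth is that recruitment will be re-evaluated periodically. That process compares actual with projected dialysis starts. It steers towards the same 152 and would not recover power lost to the choice of method.

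Finally, a conservative interval is valid and protects the type I error. That is true, and keeping it is acceptable provided the stated power matches.

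**Conclusion.** The point holds in conditional form. The figure of 152 is not an arithmetic error: standard approximations reproduce it. What is badly fixed is the link between that figure and the analysis. Of the two permitted measures, the risk difference with a chi-square or score analysis delivers the stated power (about 81%). The odds ratio with the usual conditional exact interval does not: about 76%, with a true error of about 3.3%, and 170 starters needed for 80%. Under the design effect the Wald risk difference and the exact odds ratio disagree in about 5% of trials.

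These figures assume 1:1 allocation, 76 starters per arm, rates of exactly 28% and 50%, and a comparison among starters. The shortfall of about 4 points is modest.

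A reader might also add the loss of power that comes from the Outcomes section counting participants who never start dialysis as non-home outcomes. That arises from the definition of the outcome, whichever interval method is used. It is a separate issue and no part of the 4 points here.

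**What to change.** State in Statistical considerations, or in the final analysis plan before unblinded access, which single measure and method decide the primary comparison. Preferred: the absolute risk difference, the scale the trial is powered on, with a score-type 95% interval such as Miettinen-Nurminen. Replace the either/and-or wording, and label any odds ratio as supportive, with a mid-P interval. Alternatively, if the conditional exact interval is kept as the decision rule, restate the power among 152 starters as about 76%.

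Either version costs one or two sentences and no additional patients. Keeping the conditional exact rule and also keeping 80% power would instead require about 170 starters.

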### Intervention

Participants in both the usual care and IHCA arms continue to be seen in the CKD clinic as part of usual care. Participants randomized to the IHCA arm will be logged in to the website during the randomization visit and provided an orientation session to familiarize them with the website. They are asked to generate their own password and encouraged to log on to the website regularly. Email reminders to log-in are sent periodically and the frequency of participants’ visits monitored. The website was developed with a view to ensure easy navigation for participants, while providing content that encompasses informational and social support to reduce conflict and uncertainty in ESRD therapy decision-making. The informational support component of the website includes a section for *Frequently Asked Questions*, demonstration videos, and still photographs of equipment, as well as pre-recorded video interviews with local experts and existing patients. Updated information will continue to be added by a variety of content-expert healthcare professionals as it comes available. The social support component of the website will include video and text narratives of patients addressing the benefits and challenges of home dialysis, and a moderated forum for participants to discuss issues surrounding home dialysis with current home dialysis patients. Participants will also have the opportunity to email “experts,” including nephrologists, nurses, and existing home dialysis patients with any questions they may have. The available resources are available to all participants randomized to the intervention group, regardless of their intended modality.

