### Outcomes

The primary outcome is the proportion of participants who receive any dialysis using a home-based therapy (PD or HHD) within 3 months of dialysis initiation. Participants that do not start dialysis or who receive a pre-emptive transplantation at study close will be regarded as non-home-based dialysis outcomes. Participants for which a modality cannot be ascertained will be considered non-home dialysis outcomes. Secondary outcomes include (1) proportion of patients intending to perform a home-based dialysis at 1 year, (2) dialysis knowledge as measured using a locally developed assessment tool (available online as Additional file 1), (3) decision conflict measured using the Decisional Conflict Scale [20], and (4) level of social support measured with the Duke-UNC Functional Social Support Questionnaire [21]. All of the above outcomes will be measured at baseline and 6 and 12 months post intervention.

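### The primary comparison is crude, and the covariate list for the sensitivity analysis leaves out baseline intended modality and site, so some precision is lost

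*Protocol article*

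**What the plan says.** All references are to the protocol article.

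- **Primary comparison.** Statistical considerations expresses differences in frequencies as absolute risk differences and/or odds ratios with 95% confidence intervals. No covariate is named.
- **Adjustment.** It appears only as a sensitivity analysis, "assessing the treatment effect after adjusting for baseline risk factors of known or highly suspected association with modality choice". The list, in order, is age, sex, diabetes, socioeconomic strata, caregiver availability, cognition, frailty, health literacy and other comorbidity. At most one variable per 12 home-dialysis events may enter, in that order.
- **Baseline intention.** Outcomes lists as a secondary outcome the "proportion of patients intending to perform a home-based dialysis at 1 year" and then states: "All of the above outcomes will be measured at baseline and 6 and 12 months post intervention". On its natural reading, intention is recorded at baseline.
- **Site.** Study design and randomization stratifies allocation by site. Site is in neither the main comparison nor the covariate list.
- **Sample size.** "The baseline probability of selecting home-based dialysis is assumed to be 28 % based on local data"; the design has "80 % power to detect a 22 % absolute difference between the intervention and usual care groups", and "it is estimated that 152 participants would need to initiate dialysis to detect a significant difference between groups". The recruitment target is 264.
- **Scope to change.** The analyses may be modified in the final analysis plan before unblinded data access.

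**The concern.** Under Table 1, participants have already received modality education and have declared an intent for dialysis or transplant. What a person says at baseline about home dialysis plausibly predicts whether they later start it, so it fits the article's own criterion for choosing covariates. Leaving it out means that variation in the outcome which the trial could explain stays in the standard error.

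This goes beyond detail deferred to an analysis plan, because the article itself fixes a named list, an order and a cap. As that list stands, no number of events brings intention into the model. Leaving out site has a similar cost: an analysis that ignores a stratification factor tends to give standard errors that are somewhat too large when site is related to the outcome.

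At stake is a modest amount of power and interval width. The validity of the result is not in question.

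**Working it through.** **1. The plan's own figure.** Inputs from Statistical considerations: 28% in control, 50% with the intervention (28 + 22), two-sided alpha 0.05, power 80%. Equal allocation is assumed, since the article gives no ratio. With the pooled proportion 0.39:

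n per arm = [1.960·√(2·0.39·0.61) + 0.842·√(0.28·0.72 + 0.50·0.50)]² / 0.22² = 75.97, so 76 per arm and 152 in total.

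The stated 152 reproduces exactly, and it is the size for a crude two-proportion test.

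**2. What the cap admits.** Expected home-dialysis events: 76·0.28 + 76·0.50 = 59.3. Then 59.3/12 = 4.9, so four variables enter: age, sex, diabetes and socioeconomic strata. A sixtieth event would admit caregiver availability, but still not intention.

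**3. Crude power over all randomised.** Outcomes counts participants who do not start dialysis as non-home. If 152 of 264 start (57.6%), the rates are 0.28·0.576 = 16.1% and 0.50·0.576 = 28.8%, a difference of 12.7 points. With 132 per arm the variance is (0.161·0.839 + 0.288·0.712)/132 = 0.002578, SE 0.0508. Power = Φ(0.1267/0.0508 − 1.960) = 70.4% (69.6% with the pooled formula).

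**4. Gain from adjustment.** The link between intention and modality is not in the article, so it is assumed: 30% to 50% intend home at baseline, the odds ratio of intention for a home start is 2 to 16 and the same in both arms, and starting dialysis is unrelated to intention. Let q be the share intending home, and let c1, c0 (control) and t1, t0 (intervention) be the home rates in those who do and do not intend it. The large-sample variance of the standardised risk difference is

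{q[c1(1−c1) + t1(1−t1)] + (1−q)[c0(1−c0) + t0(1−t0)]}/n + q(1−q)[(t1−c1) − (t0−c0)]²/(2n).

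Example with q = 0.40 and odds ratio 4. Among starters the rates are 44.8% and 16.8% in control, 69.9% and 36.7% with the intervention. Multiplied by 0.576 they become 0.258, 0.097, 0.402 and 0.211. The variance is 0.002465, SE 0.0496, a cut of 4.4%. Power = Φ(0.1267/0.0496 − 1.960) = 72.3%.

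Ranges over q = 0.30 to 0.50:

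| Odds ratio of intention | All 264: variance cut | All 264: power, from 70.4% | 152 starters: variance cut | 152 starters: power, from 81.4% |
|---|---|---|---|---|
| 2 | about 1% | about 71% | 2–3% | about 82% |
| 4 | about 4% | about 72% | 9–10% | about 85% |
| 8 | 8–9% | about 74% | 19–20% | about 89% |
| 16 | 13–14% | 76–77% | 29–31% | 92–93% |

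The starters column begins at 81.4% rather than 80.0% because these comparisons use the unpooled variance. Unrounded, the gain runs from about 0.5 to 6 points over all 264, and from about 1 to 12 points among starters. Any gain from adding site is not included.

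**The case against.** The strongest reply is that nothing here is an error. A crude comparison by allocated group is unbiased under randomisation, the 152 was computed for exactly that comparison, and the article lets the final analysis plan change the analyses. All of this stands, and it limits the point to efficiency. It does not remove the point, because the article commits to an ordered list and the list omits a collected variable that meets its own criterion.

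Four stronger readings are tempting, and the article does not support them.

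- *Chance imbalance in intention undermines the primary result.* The crude interval and p value ("A two-sided *p* value of <0.05 will be regarded as significant") already allow for chance imbalance in any covariate.
- *Intention is known to be the most direct predictor.* This is a reasonable judgement, but no figure supports it, and the Discussion leaves open which baseline factors, if any, predict home dialysis.
- *Transplant intent is scored as a failure.* Outcomes scores receiving a pre-emptive transplant, or not starting dialysis, as non-home. Someone who intended transplant and starts home dialysis is a success. Likewise, the statement that resources are "available to all participants randomized to the intervention group, regardless of their intended modality" concerns website access within one arm; enrolment is governed by Table 1.
- *The power of about 70% over all randomised results from not adjusting.* It comes from counting non-starters as non-home. That is a separate and larger matter, and adjustment recovers only a small part of it.

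**Conclusion.** The point holds as a loss of precision. The main comparison is crude, and the sensitivity list omits both baseline intention and the stratification factor. The direction is secure if intention predicts modality at all. The size is not: the odds ratios and the share intending home are assumptions, and at an odds ratio of 2 the gain over all randomised is about half a power point. If starting dialysis is itself related to intention, the figures over all 264 would differ. The gain applies to a standardised risk difference. A conditional odds ratio can gain power without a narrower interval. The change is worth making because it costs almost nothing, but the trial is interpretable without it.

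**What to change.** Before any unblinded data access, the analysis plan should:

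1. Define the primary analysis as an absolute risk difference adjusted for site and baseline intended modality (home versus not home), standardised from a logistic model, with its 95% confidence interval. State where undecided participants are placed.
2. Report the crude risk difference as supportive.
3. Put baseline intention first in the covariate order of the sensitivity analysis.

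With three sites, the primary model has two site terms and one intention term beyond arm, so three; a separate level for transplant intent makes four. Both fit the plan's own limit of about four at 59 events. If the intervention had no effect, 152·0.28 = 42.6 events would allow only three, and added sites would add terms, so the coding should be settled with that in mind.

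The cost is slightly more analysis work and no new data. The drawback is that socioeconomic strata, fourth on the list, may drop out of the capped sensitivity model when intention goes first.

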## Methods/design

### Study design and randomization

The study is a multi-centered randomized controlled trial comparing the use of a secured web-based IHCA (website www.independentdialysis.ca) versus usual care in the promotion of home-based dialysis therapies. A participant flow diagram is shown in Fig. 1. Randomization is performed using a computer-generated sequence in variable blocks, stratified by site and allocation occurring using sequentially numbered sealed opaque envelopes. Each study participant will be assigned a unique number. The information about randomization sequence and block size will be kept confidential.

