### Participants

All eligible participants are identified by the local CKD clinic electronic database and screened for eligibility by CKD nurses in the circle of care. All eligible participants are then approached and asked if they are interested in speaking to research staff about the study. Consented participants are then randomized into one of two study arms: (1) usual care or (2) the IHCA. The participant inclusion and exclusion criteria are shown in Table 1.

**Table 1 Tab1:** Patient inclusion and exclusion criteria

Inclusion criteria	Exclusion criteria
1. Age ≥18 years 2. Enrolled in CKD clinic 3. Previously received ESRD modality education 4. Personal access to a home computer with Internet access 5. Most recent eGFR ≤20 ml/min/1.73 m^2^ 6. Declared intent for either dialysis or transplant	1. Absolute medical contraindication to home-based dialysis 2. Inability to provide informed consent 3. Inability to use a home computer and Internet 4. Inability to understand English (written and spoken) 5. Severe visual or auditory impairment

Abbreviations: *CKD* chronic kidney disease, *ESRD* end-stage renal disease, *eGFR* estimated glomerular filtration rate, *ml* milliliters, *min* minutes, and *m*
^*2*^ meter squared

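### Minor: the primary outcome depends first on reaching dialysis, but the ordered, capped covariate list leaves no place for baseline eGFR, at a modest cost in precision

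*Protocol article*

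**What the plan says.** All references are to the Protocol article.

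- **Outcomes** defines the endpoint: "The primary outcome is the proportion of participants who receive any dialysis using a home-based therapy (PD or HHD) within 3 months of dialysis initiation". It then fixes how those without dialysis count: "Participants that do not start dialysis or who receive a pre-emptive transplantation at study close will be regarded as non-home-based dialysis outcomes".
- **Statistical considerations** sets the analysis population: "participants randomized will be analyzed according to the group to which they were allocated". Non-starters therefore stay in the denominator.
- **Participants, Table 1** requires "Most recent eGFR ≤20 ml/min/1.73 m^2", with no lower limit. A value is on hand for every participant before randomisation.
- **Statistical considerations** plans sensitivity analyses "adjusting for baseline risk factors of known or highly suspected association with modality choice". The list reads: "These factors will include age, sex, diabetes mellitus status, socioeconomic strata, availability of a caregiver, presence of cognitive impairment", followed by "frailty [23], health literacy [24], and other comorbidities". Variables are taken in that order, with no more than one for every 12 home-dialysis events.
- The same section assumes 28% home dialysis under usual care, a 22-point absolute difference, 80% power, 152 dialysis starters and 264 recruits. It allows the analyses to be changed in the final analysis plan before unblinded access to data.

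**The concern.** A participant can count as a home-dialysis success only by starting dialysis before study close. Baseline eGFR is an obvious candidate for predicting that step, because it reflects how near each person is to needing dialysis. The covariates are selected for their link with modality choice, which is the second step only. eGFR is not named, and other comorbidities does not reasonably cover it. Even on a generous reading, that item comes last in a list that the cap cuts short.

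Two things are at stake. First, if the arms differ by chance in nearness to dialysis, one arm will tend to have more starts and hence more home outcomes, and no listed adjustment uses the value that would help a reader judge this. Second, outcome variance that a recorded value could explain stays in the comparison.

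**Working it through.** **1. Reproduce the plan's figure.** Inputs: 28% vs 50%, two-sided 0.05, 80% power. Allocation 1:1 is an assumption, since the ratio is not stated.

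n per arm = [1.96·√(2·0.39·0.61) + 0.8416·√(0.28·0.72 + 0.50·0.50)]² / 0.22² = (1.352 + 0.566)² / 0.0484 ≈ 76, total **152**. The plan's number reproduces.

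**2. Outcome on the all-randomised scale.** Start fraction = 152/264 = 57.6%, so 42.4% do not start. Home rates: 0.576·28% = 16.1% and 0.576·50% = 28.8%; difference 12.7 points.

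Standard error with 132 per arm = √[(0.161·0.839 + 0.288·0.712)/132] = 5.1 points. Power is about 70% (69.6% with the pooled test).

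**3. Covariate slots.** Expected home events = 76·0.28 + 76·0.50 = 59.3. Then 59.3/12 = 4.9, so four variables: age, sex, diabetes status, socioeconomic strata.

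**4. What eGFR adjustment would gain.** The document gives no association between eGFR and starting dialysis, so a range is assumed. Simulation: 10,000 trials per setting, 264 randomised 1:1, eGFR uniform, logistic start probability averaging 57.6%, home use among starters 28% vs 50%.

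| Start OR per SD lower eGFR | Power, unadjusted | Power, adjusted | Fall in variance of risk difference | Shift in unadjusted difference from a 1-SE eGFR imbalance |
|---|---|---|---|---|
| 1.5 | 70.3% | 70.7% | about 0% | 0.5 points |
| 2 | 70.3% | 71.4% | about 2% | 0.7 points |
| 3 | 70.4% | 72.6% | about 4% | 1.1 points |
| 4.5 | 69.6% | 73.0% | about 6% | 1.3 points |
| 7.4 | 70.5% | 74.9% | about 9% | 1.6 points |

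One standard error of the between-arm difference in mean eGFR is √(2/132) = 0.123 SD.

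**5. Closed-form check at OR 4.5.** With X the standardised eGFR (higher = lower eGFR) and p(X) the start probability, numerical integration gives E[X·p(X)] = 0.282. The common slope of the outcome on X is 0.39·0.282 = 0.110.
- Shift from a 1-SE imbalance: 0.110·0.123 = 1.35 points.
- Variance sum: 0.340 unadjusted; 0.340 − 2·0.110² = 0.316 adjusted, a fall of 7%.
- Power: Φ(12.67/5.08 − 1.96) = 70%; adjusted standard error √(0.316/132) = 4.89 points, Φ(12.67/4.89 − 1.96) = 73.5%.

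The same calculation gives variance reductions of about 1% at OR 1.5 and just under 10% at OR 7.4, hence the quoted range of 1 to 10%.

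**6. Second simulation.** Logistic regression, normally distributed eGFR, 2,000 runs per setting, simulation error about 1 point. At OR 1.5 / 2 / 3 / 5, power moves from 69.7 to 70.4, 69.5 to 70.9, 68.3 to 70.7 and 68.7 to 71.4%. The mean risk difference is 0.126 to 0.127 with or without eGFR, so omitting it causes no bias.

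**The case against.** The strongest reply is that nothing here is an error. Randomisation makes the comparison unbiased, and the unadjusted interval and p value already allow for chance imbalance in every prognostic factor, eGFR included. A 1-SE imbalance shifts the difference by at most 1.6 points in the table, about a third of its 5.1-point standard error. The gain rests on assumed associations, and at the weaker ones it is under 1.5 points. Follow-up is stated as at least one year, so it may differ between participants and weaken the link between eGFR and starting. Giving eGFR a slot displaces a factor that the investigators chose, and nothing shows that eGFR is worth more. The article also leaves the analyses open to change in the final analysis plan.

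All of that stands, and it sets the weight of the point. It does not remove it: the article states the list, the order and the cap, and as written they exclude a predictor suited to the first step of the outcome.

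Three stronger readings are tempting and are not supported:
- **That the result would be biased.** It would not, as the unchanged mean difference shows.
- **That stratifying by site alone is a defect.** The article says "Randomization is performed using a computer-generated sequence in variable blocks, stratified by site". That is an acceptable scheme, and covariate adjustment deals with eGFR without changing it.
- **That eGFR adjustment would restore the planned power.** The fall from 80% to about 70% comes from sizing on starters while scoring non-starters as failures. That is a separate matter, which adjustment does not repair.

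**Conclusion.** The point holds as a minor, cheap improvement. The covariates match modality choice but not the outcome as defined, which about 42% of participants are expected to fail by not starting dialysis.

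The loss is limited to precision and to a check on chance imbalance: about 1 to 10% of the variance of the risk difference, about 0.5 to 4 points of power from a base of about 70%, and a shift of about 0.5 to 1.6 points for a 1-SE imbalance, against an expected difference of 12.7. These figures assume 1:1 allocation, the plan's own rates and start fraction, and eGFR-to-start odds ratios of 1.5 to 7.4 per SD, for which the document gives no value.

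The power gain arises only if eGFR enters the primary comparison. In the sensitivity model alone, it serves as a check and leaves the primary power unchanged.

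**What to change.** Before any unblinded access to data:

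1. Adjust the primary between-group comparison for screening eGFR as a continuous variable, and report the unadjusted result alongside. If the primary comparison is to stay unadjusted, place eGFR first in the ordered covariate list; adding it at the end would have no effect under the cap.
2. Report the proportion starting dialysis by arm, so that a difference in starts can be told apart from a difference in modality among starters.

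The cost is a line or two of wording. The value is already obtained at screening, and randomisation is untouched. In the capped sensitivity model, eGFR takes one slot: at about 59 home events it displaces socioeconomic strata. If the website had no effect, 152·0.28 = 42.6 events would allow only three variables (42.6/12 = 3.5), and eGFR in first place would displace diabetes status as well. The investigators should accept that trade-off knowingly.

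### The sample size is set among dialysis starters, but the primary outcome counts everyone randomised; at the planned 152 starts in 264, power is about 70%, not 80%

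*Protocol article*

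**What the plan says.** Under Statistical considerations, the protocol article gives the inputs: "The baseline probability of selecting home-based dialysis is assumed to be 28 % based on local data", and "80 % power to detect a 22 % absolute difference between the intervention and usual care groups". It concludes that "it is estimated that 152 participants would need to initiate dialysis to detect a significant difference between groups". Recruitment of 264, with at least one year of follow-up, is then justified from local transition rates, so that enough participants start dialysis. The same section adds: "This recruitment target will be re-evaluated periodically and adjusted as needed based on differences between projected and when actual dialysis starts".

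The Outcomes section defines the primary outcome so that non-starters remain in it as failures: "Participants that do not start dialysis or who receive a pre-emptive transplantation at study close will be regarded as non-home-based dialysis outcomes". Participants whose modality cannot be established are scored the same way. Statistical considerations sets the analysis population: "In all analyses, participants randomized will be analyzed according to the group to which they were allocated".

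**The concern.** The two sections use different denominators. The 152 is a count of starters, and the 28% and 22-point inputs apply to starters. The primary comparison is made in all 264 randomised, of whom 264 − 152 = 112 are expected not to start and are scored as not on home dialysis. Adding people who cannot be successes lowers both arms' proportions and shrinks the absolute difference. The article does not carry its assumptions over to that denominator.

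What is at stake is the stated power and the recruitment target. If the assumed effect among starters is real, the planned primary analysis would miss it about 30% of the time instead of 20%. The number watched during recruitment, 152 starts, would also be too low for the outcome as defined.

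**Working it through.** **Inputs from the protocol article:** alpha 0.05, two-sided; power 80%; 28% versus 50% (28 + 22); 152 starters; 264 randomised.

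**Assumptions not in the article:** 1:1 allocation; the same start share in both arms, 152/264 = 57.6%; no unknown modality among starters (any would lower power further).

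**Step 1. Reproduce the 152.** Two proportions, pooled variance under the null, no continuity correction, with p̄ = (p1 + p2)/2:

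n per arm = [1.960 √(2p̄(1−p̄)) + 0.842 √(p1(1−p1) + p2(1−p2))]² / (p2−p1)²

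With p1 = 0.28, p2 = 0.50 and p̄ = 0.39: (1.352 + 0.566)² / 0.22² = 75.97. That is 76 per arm, 152 in total, with power 80.0%. The article's figure reproduces exactly as a starters-only calculation.

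**Step 2. Move the same effect to all randomised.**
- Usual care: 0.28 × 152/264 = 16.1%
- Intervention: 0.50 × 152/264 = 28.8%
- Difference: 0.22 × 152/264 = 12.7 points

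**Step 3. Power with 132 per arm.**

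z = [(p2−p1) − 1.960 √(2p̄(1−p̄)/n)] / √([p1(1−p1) + p2(1−p2)]/n)

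With p̄ = 0.2245 and n = 132: (0.1267 − 0.1007) / 0.0508 = 0.512, so power is Φ(0.512) = 69.6%. Exact enumeration of the uncorrected chi-square test gives 70.1%, and the unpooled formula 70.4%.

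**Step 4. What 264 can detect with 80% power.** Keeping usual care at 16.1% and solving Step 3 for 80% gives a difference of 14.5 points (16.1% versus 30.7%). Among starters this is 14.5/0.576, or about 25 points.

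**Step 5. What would give 80% for the assumed effect.**
- At the same start share, the Step 1 formula with 16.1% and 28.8% gives 169.2. That is 170 per arm, 340 randomised, with 340 × 0.576 ≈ 196 starts.
- With 264 kept, the start share must be higher. Power is 76.4% if 65% start and 80.5% if 70% start (0.70 × 264 ≈ 185 starts).

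**Step 6. The recruitment rule when starts lag.** Each row fixes a start share and compares staying at 264 with recruiting until 152 have started.

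| Start share | Power at 264 | N giving 152 starts | Power at that N |
|---|---|---|---|
| 57.6% | 69.6% | 264 | 69.6% |
| 50.7% | 62.5% | 300 | 68.0% |
| 44.7% | 55.9% | 340 | 66.8% |
| 33.8% | 43.0% | 450 | 64.5% |

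The rule recovers power in every row where starts lag, but no row reaches 80%.

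**The case against.** **More than 152 may start.** The 57.6% is derived from 152/264, not stated. Follow-up is at least a year and outcomes are scored at study close, so early recruits may be followed for longer. This stands as a condition on the figure: about 185 starts among 264 would bring power to 80%. But 152 is the article's own target, and nothing requires the trial to go beyond it.

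**The 28% and 50% may have been meant for all randomised.** Then 152 randomised would be enough, and 264 would give 96% power. The text does not support this reading: it ties 152 to people starting dialysis and explains 264 by the rate at which clinic patients reach end-stage therapy.

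**The analysis plan may settle it.** The point does not rest on an omission. The outcome definition and the power statement in this one document do not fit together.

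Three stronger readings are tempting and should not be drawn:
- *The recruitment rule makes matters worse by diluting the proportions.* It does not. A low start share does the diluting, whether or not anyone is added. At a given start share, extra recruits raise power, as Step 6 shows. The fault is that the rule's target is too low.
- *Power is only about 65% because the plan names an exact test.* A Fisher-type test does give 65.2%, but the article attaches its exact method to the confidence interval for the odds ratio. It names no exact test for the primary comparison.
- *The result will be judged against 22 points.* The article uses 22 points for sizing only, not as a threshold for interpretation.

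**Conclusion.** The point holds as a mismatch between the basis of the sample size and the denominator of the primary outcome. It is not an arithmetic slip, since 152 is correct for the question it answers. At the planned 152 starts among 264 randomised, the primary analysis has about 70% power for the assumed effect, 10 points below the stated figure. The shortfall depends on the assumptions listed in the working, and it closes only if about 70% of those randomised start dialysis. Recruiting until 152 have started does not close it at any start share examined.

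**What to change.** Keep the all-randomised outcome; it preserves the randomised comparison and avoids selecting on a post-randomisation event. Then make two changes under Statistical considerations:

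1. Restate the power on that denominator: 16.1% versus 28.8%, 132 per arm, about 70% power, with about 14.5 points overall detectable at 80%. State the assumed start share and allocation ratio.
2. Base the recruitment review on the all-randomised home-dialysis proportion, pooled over both arms and blinded, together with the number randomised, instead of on reaching 152 starts.

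The cost is rewording and a less favourable power figure; neither change in itself requires more participants. If the sponsor wants 80% at the same start share, the corresponding size is about 340 randomised (about 196 starts), which is 76 more than planned. Alternatively, if follow-up beyond one year is expected to yield about 185 starts among 264, the article should say so and make that the target.
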